### Secondary

- Incidence of DLTs.
- Incidence of IRTs
- Incidence of nephrotoxicity and hepatotoxicity
- Number of AEs and SAEs
- Laboratory values for different parameters

# 11. STUDY DESCRIPTION (INVESTIGATIONAL PLAN)

## 11.1 Basic Principles and Ethical Considerations

The study will be performed in accordance with the Standard Operating Procedures (SOPs) laid down by SIRO Clinpharm Pvt. Ltd. These SOPs have been developed in accordance with International Conference on Harmonization (ICH) for Good Clinical Practice (GCP); GCPs for Clinical Research in India, 2001; Indian Council of Medical Research (ICMR) Ethical Guidelines for Biomedical Research on Human Participants, 2006 and Schedule Y, Amended 2005 under Drugs and Cosmetics Act and Rules there under, which are consistent with the Ethical Guidelines outlined in Declaration of Helsinki, version 1996 (*Appendix A)*. The study will commence only after the approval of the IRB/IEC.

## 11.2 Sample Size

Considering an estimated difference in proportions of patients achieving definitive cure for Amphomul^®^ vs. AmBisome equals to zero and non-inferiority margin fixed at -0.10, a sample size of 400 patients in ratio of 3:1 in Amphomul^®^ and AmBisome treatment groups (i.e. 300 patients in Amphomul^®^ and 100 patients in AmBisome) is required to assure at least 80% power for the non-inferiority test. Considering a total drop out rate after baseline and major protocol deviations close to 20%, 500 patients (i.e. 375 patients in Amphomul^®^ and 125 patients in AmBisome) will be enrolled in the study.

## 11.3 Study Design

The study will be prospective, two‑arm, randomized, open-label, multicenter, Phase III clinical study. Patients will be randomized to receive infusion of Amphomul emulsion (15 mg/kg as a single dose infusion) administered over 4 to 6 hours or AmBisome 15 mg/kg as single dose infusion over 4 to 6 hours

Only patients for whom the Investigator believes the requirements of the protocol will be complied with should be enrolled in the study.

## Flow of events for the study

##

Signed Informed consent Form,

rK39 dipstick test will be performed prior to any screening procedure Screening

Eligible patients will be randomized to receive EITHER Amphomul® 15 mg/kg as a single dose infusion OR AmBisome 15 mg/kg as a single dose infusion.

Drug will be administered to all the patients on Day 1 over 4 to 6 hours (dose of Amphomul® is 15 mg/kg)

Comparator drug, AmBisome 15 mg/kg administered on Day 1 over 4 to 6 hours.

Patients will be discharged from the hospital on Day 7

Follow-up visit on Day 30: if splenic aspirate score is 0 initial cure achieved, if score is +1 splenic aspiration repeated on Day 45, if the score is above +1 patient considered as treatment failure and discontinued from the study.

At follow-up on Day 45 if splenic aspirate score is 0, initial cure achieved and follow up at 6 months (after the administration of study drug), if the score is +1 and above patient will be considered treatment failure and withdrawn from the study.

End of study visit will be done at 6 months after study drug administration. Definitive cure is achieved if initial cure at Day 30 or 45, followed by no clinical signs and symptoms of Visceral Leishmaniasis at 6 months (after the administration of study drug)

Figure 1: Efficacy and Safety assessment across visits

Period of Hospitalization

Follow up visits

Day 30 Day 45 * 6 months**

Screening Day 1 Day7

V 0 V1 V 2 Additional V3 (EOS)

Visit

*Day 45 Visit is only for patients with splenic aspirate score +1 on Day 30.

**Follow-up visit at 6 months after study drug administration (EOS Visit).

## 11.5 Study Duration, Treatment Interruption and Termination

The clinical part of the study will start after the approval of the responsible IRB/IEC and after the site initiation visit is performed.

The timeframes of the study will be as follows:

- Total duration of the Clinical study: 1 year 8 months
- Total Clinical Duration (maximum) per patient: 7 months
- Recruitment Period (all patients): 7 months
  - - - **Study Treatment Interruption:**
- In case of infusion related reactions temporary discontinuation of the infusion or administration of concomitant medications as judged appropriate by the investigator, (other than prohibited medications) will be permitted.
- None of the patients will be replaced.

**The entire study may be prematurely terminated/discontinued** if there is,

- Comprehensive deficiency in the recorded data or protocol compliance so that the results of the study cannot be reliably assessed.
- The Sponsor, PI(s) and the Project Manager, if appropriate commonly decide premature termination, after consultation with the Ethics Committee and the study sponsor.

In the event of early termination, PI(s) will cease use of the IP immediately. All outstanding Case Report Forms (CRFs) will be completed and returned to SIRO together with completed drug inventory, records and remaining trial material.

A written statement fully documenting the reasons for such a termination will be provided from Bharat Serums and Vaccines Ltd. to the IRB/IEC and Drugs Controller General of India (DCGI).

# 12. STUDY POPULATON

## Sample size

Considering a drop-out rate of 20%, 500 patients will be enrolled to get 400 evaluable patients

Considering an estimated difference in proportions of patients achieving definitive cure for Amphomul^®^ vs. AmBisome equals to zero and non-inferiority margin fixed at -0.10, a sample size of 400 patients in ratio of 3:1 in Amphomul^®^ and AmBisome treatment groups (i.e. 300 patients in Amphomul^®^ and 100 patients in AmBisome) is required to assure at least 80% power for the non-inferiority test. Considering a total drop out rate after baseline and major protocol deviations close to 20%, 500 patients (i.e. 375 patients in Amphomul^®^ and 125 patients in AmBisome) will be enrolled in the study.

## Target Population

Patients of either gender, between 5 and 65 years of age (both inclusive) with Visceral Leishmaniasis (Kala-azar).

## Inclusion Criteria

Following patients will be included in the study -

1. Male or female patients aged between 5 to 65 years (both inclusive).
2. Patient/patient’s LAR/impartial witness is willing and able to give written informed consent to participate in the study.
3. Clinical signs and symptoms of Visceral Leishmaniasis (fever of over 2 weeks duration and splenomegaly)
4. Presence of amastigotes (*Leishmania donovani* bodies) at prescreening detected by rK39 dipstick test with confirmation of Kala-azar by splenic or bone marrow aspirate smear examination.
5. No previous treatment for Visceral Leishmaniasis within 30 days from screening.
6. Non-pregnant, non-lactating females of age ≥5 years, and woman of childbearing potential (any woman who has reached menarche) who are willing to use acceptable methods of contraception like long term acting injections ex. Depo‑Provera.
7. Negative UPT in all women physiologically capable of becoming pregnant (any woman who has reached menarche)
8. Hemoglobin ≥5 g/dL.
9. WBC count ≥ 1000/ cmm,
10. Platelet count ≥ 50000/cmm.
11. ALT, AST and alkaline phosphatase ≤2.5 times the ULN.
12. Prothrombin time ≤4 seconds above the control
13. Normal serum potassium levels
14. Negative tests for HIV, HCV and HBsAg

## Exclusion Criteria

Patients who meet any of the following criteria at screening or prior to treatment assignment have to be excluded from study entry:

1. Patients with past history of treatment with Amphotericin B or any other drug for Visceral Leishmaniasis within 30 days prior to screening.
2. Patients positive for HIV, HCV and HBsAg infection, immunocompromised patients (through history).
3. A history or evidence of any concurrent disease that may be serious or life threatening, significant hematological, cardiac, hepatic, renal, respiratory, neurological or metabolic disease or any condition which, in the opinion of the investigator, may constitute a safety concern or interfere with the evaluation of the study objectives or may prevent the patient from the completing study therapy or subsequent follow-up may have a significant impact on the outcome of the study.
4. Concurrent diabetes, tuberculosis or bacterial pneumonia (on chest X-ray, ESR at screening, past history) or any other infectious or major psychiatric disease.
5. Patients with concurrent Malaria will not be included in the trial. Parascreen antigen test for detection of malarial parasites will be performed at screening visit. Patients diagnosed with malaria could be rescreened for enrollment in the trial after adequate treatment of Malaria; & if the parascreen antigen test for detection of malarial parasites is found negative then the patient could be enrolled in the trial
6. History of major surgery within 2 weeks prior to screening.
7. BUN and serum creatinine >1.5 times ULN, and serum total bilirubin >1.5 times ULN
8. Proteinuria ≥2+
9. Pregnant or nursing women.
10. History of alcoholism or illicit drug use/ abuse, or any condition associated with poor compliance.
11. Known hypersensitivity to Amphotericin B, inactive ingredients of Amphomul^®^ formulation, inactive ingredients of AmBisome formulation.
12. Patients receiving any of the medications prohibited by the study protocol.
13. Simultaneous participation in another trial or received any IP <30 days prior to enrolment.
14. Any condition which in the investigator’s opinion may prevent the patient from completing the study therapy or follow-up

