**Criteria for Exclusion:**

Patients who meet any of the following criteria at screening or prior to treatment assignment have to be excluded from study entry:

1. Patients with past history of treatment with Amphotericin B or any other drug for Visceral Leishmaniasis within 30 days prior to screening.
2. Patients positive for HIV, HCV and HBsAg infection, immunocompromised patients (through history).
3. A history or evidence of any concurrent disease that may be serious or life threatening, significant hematological, cardiac, hepatic, renal, respiratory, neurological or metabolic disease or any condition which, in the opinion of the investigator, may constitute a safety concern or interfere with the evaluation of the study objectives or may prevent the patient from the completing study therapy or subsequent follow-up may have a significant impact on the outcome of the study.
4. Concurrent diabetes, tuberculosis or bacterial pneumonia (on chest X-ray, erythrocyte sedimentation rate (ESR) at screening, past history) or any other infectious or major psychiatric disease.
5. Patients with concurrent Malaria will not be included in the trial. Parascreen antigen test for detection of malarial parasites will be performed at screening visit. Patients diagnosed with malaria could be rescreened for enrollment in the trial after adequate treatment of Malaria; and if the parascreen antigen test for detection of malarial parasites is found negative then the patient could be enrolled in the trial.
6. History of major surgery within 2 weeks prior to screening
7. Blood urea nitrogen (BUN) and serum creatinine >1.5 times ULN, and serum total bilirubin >1.5 times ULN
8. Proteinuria ≥2+
9. Pregnant or nursing women
10. History of alcoholism or illicit drug use/ abuse, or any condition associated with poor compliance
11. Known hypersensitivity to Amphotericin B, inactive ingredients of Amphomul^®^ formulation, inactive ingredients of AmBisome formulation.
12. Patients receiving any of the medications prohibited by the study protocol.
13. Simultaneous participation in another trial or received any IP <30 days prior to enrolment.
14. Any condition which in the investigator’s opinion may prevent the patient from completing the study therapy or follow-up.

Visits and Assessments Done

Screening visit Visit 0 (Day ‑7 to Day 0)

- Informed consent will be obtained.
- Detailed physical examination
- Vital signs will be recorded
- Prescreening rK39 dipstick test

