**Nephrotoxicity**

- This would be the main criterion for the analysis of safety and would be defined as grade 3 or higher increase in serum creatinine level, which will be considered as a DLT.
- However, non-DLT rise of >2 times baseline, or, a value >2 mg/dL, whichever is more, shall also be considered for overall evaluation of nephrotoxicity due to the study drug.
- Serum creatinine shall be monitored for this purpose on Day 7 of hospitalization and during subsequent visits till the end of first month.

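### Exclusion 7 joins BUN, creatinine and bilirubin with 'and', so an isolated raised creatinine or BUN is not caught by any numeric entry limit and is left to investigator judgement

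*Protocol*

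**What the plan says.** The exclusion list in Section 12.4 opens with "Patients who meet any of the following criteria at screening or prior to treatment assignment have to be excluded from study entry". Item 7 of that list is "BUN and serum creatinine >1.5 times ULN, and serum total bilirubin >1.5 times ULN". The Study Summary (Section 8, Criteria for Exclusion) has the same item with the abbreviation spelled out: "Blood urea nitrogen (BUN) and serum creatinine >1.5 times ULN, and serum total bilirubin >1.5 times ULN". Both places use the same connectives and the same comma.

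Three other exclusions bear on a patient with poor renal or hepatic values. Exclusion 3 covers "significant hematological, cardiac, hepatic, renal, respiratory, neurological or metabolic disease or any condition which, in the opinion of the investigator" may raise a safety concern; it has no numeric limit. Exclusion 8 covers proteinuria of 2+ or more. Exclusion 14 is "Any condition which in the investigator’s opinion may prevent the patient from completing the study therapy or follow-up".

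On the inclusion side (Section 12.3), item 11 caps ALT, AST and alkaline phosphatase at 2.5 x ULN, item 12 limits prothrombin time and item 13 requires normal potassium. None of them mentions BUN, creatinine or bilirubin.

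Section 18.6 says of nephrotoxicity, "This would be the main criterion for the analysis of safety", and defines it from serum creatinine.

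**The concern.** In an inclusion criterion, 'and' between several limits is strict: every value must be within its limit. In an exclusion criterion the same word is lenient: every value must be outside its limit before the patient is excluded. Item 7 has the lenient form. It is also the only place where the protocol sets a numeric entry limit for BUN, creatinine or bilirubin.

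Two things are at stake. The first is patient protection: these limits exist to keep patients with impaired renal or biliary function away from a high single dose of amphotericin B, and as written they do not clearly apply to one raised value. The second is consistency. There are four centres, each using its local laboratory, and two investigators could read item 7 differently in good faith. Section 22.7 asks monitors to confirm that the eligibility criteria are properly fulfilled, which they cannot do uniformly if the item has more than one reading.

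Baseline creatinine also enters the safety endpoint. Section 18.6 counts a rise that is not a DLT against twice baseline or 2 mg/dL, whichever is greater. Once baseline exceeds 1 mg/dL, twice baseline is the greater of the two, so a higher entry value raises the level that must be reached.

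**Working it through.** The protocol gives no figure to reproduce here. The check is a truth table, followed by a search for another criterion that closes the gap.

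**Step 1. Scope of the lead-in.** The word 'any' in the opening sentence links the numbered items. It does not say how the parts of a single item combine.

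**Step 2. Readings of item 7.** Let B, C and T mean that BUN, creatinine and total bilirubin respectively exceed 1.5 x ULN.

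- Literal: B and C and T.
- Comma as separator: (B and C) or T.
- Any one: B or C or T.

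| BUN raised | Creatinine raised | Bilirubin raised | Literal | Comma | Any one |
|---|---|---|---|---|---|
| no | no | no | – | – | – |
| yes | no | no | – | – | excluded |
| no | yes | no | – | – | excluded |
| no | no | yes | – | excluded | excluded |
| yes | yes | no | – | excluded | excluded |
| yes | no | yes | – | excluded | excluded |
| no | yes | yes | – | excluded | excluded |
| yes | yes | yes | excluded | excluded | excluded |

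Of the 2 x 2 x 2 = 8 patterns, the three readings exclude 1, 5 and 7. The rows that matter are the second and third. Isolated raised BUN and isolated raised creatinine escape both the literal and the comma reading. Isolated raised bilirubin escapes only the literal one.

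**Step 3. Is there a repair elsewhere?** Exclusion 2 is a useful comparison. It reads "Patients positive for HIV, HCV and HBsAg infection" and has the same loose 'and', but inclusion 14 requires negative tests for all three infections, so a single positive result disqualifies whichever way exclusion 2 is read. Item 7 has no such mirror: inclusions 11 to 13 cover liver enzymes, prothrombin time and potassium only.

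**Step 4. What still applies.** Exclusions 3 and 14 can bar a patient with one raised value on the investigator's judgement. Exclusion 8 can bar the patient if proteinuria is present. None of these is a numeric limit on creatinine, BUN or bilirubin.

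**The case against.** The best defence is that the authors plainly meant any one value. Exclusion 2 shows that they use 'and' loosely in an exclusion, and inclusion 14 shows that there they meant any single positive. This is fair evidence of intent, but it does not settle item 7. The same list uses 'or' where one condition is enough: exclusion 4 for diabetes, tuberculosis or pneumonia, exclusion 9 for pregnancy or nursing, exclusion 10 for alcoholism or drug use. Usage is mixed, and an investigator has to apply the text as it stands.

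The second defence is that marked impairment would be stopped anyway. This largely stands. A grossly raised creatinine or bilirubin is just what exclusion 3 is for, and inclusions 11 to 13 and exclusions 8 and 14 narrow the gap further. What remains is mainly the isolated, moderate abnormality, for which the numeric limit was written.

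Four stronger inferences are tempting, and the protocol does not support them.

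- That only a patient with all three values raised is excluded. This is one reading; the comma and the repeated limit allow another.
- That a patient with one raised value necessarily gets into the trial. Exclusions 3, 8 and 14 are separate grounds for refusal.
- That such a patient could already count as nephrotoxic before dosing under the Section 18.6 rule for rises short of a DLT. With baseline b, the level to exceed is the greater of 2b and 2 mg/dL. This is at least 2b, so it is always above b.
- That the comparison between arms depends on the reading. Eligibility is settled before allocation and the randomization schedule is generated for each centre (Section 15.3), so a site's reading applies to both arms at that site.

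**Conclusion.** The point holds as a defect in a stated eligibility rule. Under both the literal and the comma reading, item 7 does not exclude a patient whose only abnormality is creatinine or BUN above 1.5 x ULN. No other criterion supplies a numeric limit, so the decision passes to investigator judgement, or to exclusion 8 where there is proteinuria. Isolated raised bilirubin is uncertain: one of the two readings excludes it.

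The size in patients is unknown. The counts in the table are combinations of conditions, not frequencies, and the protocol gives no baseline distribution of these values. BUN and creatinine are both renal measures, so the patterns should not be treated as equally likely.

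The conclusion assumes that sites follow the wording of item 7. If every site already treats any one raised value as disqualifying, nothing changes in practice, but the text does not ensure this. The sample size, the power and the primary comparison of definitive cure are not affected. The correction is still worth making, because these are the only numeric entry limits tied to the trial's main safety criterion.

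**What to change.** In both the Study Summary and Section 12.4, keep the existing limits and change the connective, so that item 7 excludes a patient with BUN above 1.5 x ULN, or serum creatinine above 1.5 x ULN, or serum total bilirubin above 1.5 x ULN, and state that any one is sufficient. In the same two lists, write exclusion 2 as HIV, HCV or HBsAg so that it agrees with inclusion 14.

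The cost is a few words by amendment under Section 21.2. No threshold moves and no test is added, since BUN, creatinine and bilirubin are already measured at screening (Sections 8 and 13). The downside is possibly a few more screen failures, at sites that have been reading the item less strictly.

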## Patient Information and Informed Consent

Written informed consent must be obtained from each patient before enrolling in the study. The method of explanation to the patient/LAR/impartial witness and obtaining their consent should comply with the ICH‑GCP Guidelines, with GCP for Clinical Research in India, 2001; ICMR’s Ethical Guidelines for Biomedical Research on Human Participants, 2006 and Schedule Y, Amended 2005 under Drugs and Cosmetics Act and Rules there under, and the ethical principles in the amended Declaration of Helsinki, whichever represents the greater protection for the individual.

The patient’s/LAR’s signature/thumb impression or Impartial witness’s signature is to confirm and document patient’s willingness to participate after having received the following information:

- The study involves research
- Study objectives
- Effects (including possible side effects and reasonably foreseeable risks or inconveniences caused to the patient*)* of the study drug and/or procedures in the study
- Possible benefits of the study drug
- Performance of the study, duration, allocation to treatment and approximate number of patients involved in the trial, additional and/or invasive procedures that patient needs to undergo
- Patient's responsibilities
- Alternative treatment possibilities
- Voluntary participation in the study and the possibility to refuse or withdraw at any stage without giving reasons and without any disadvantages for the patient
- Possibility regarding further information
- Information that it is not possible to participate in the study if the patient has participated in another clinical study during the course of the past 30 days
- Information that the patient is not permitted to simultaneously participate in another clinical study
- Recording of data and disclosure to the sponsor/sponsor representatives, the IRB/IEC or the regulatory authority
- The records identifying the patient will be kept confidential and will not be made publicly available, to the extent permitted by law.
- Information that if any new information that relates to patient’s decision regarding continuation of patient's participation in the study, if available during the course of study will be made available to the patient/LAR/ impartial witness
- The part of study that is experimental
- Contact for further information and in case of trial related injury
- Any foreseeable reasons when patients' participation in study could be terminated
  at the outset of the study the patient/LAR/impartial witness receives an information sheet (in English or a language which patient understands) containing information about the study on which the patient/LAR must consent by signature/thumb impression and impartial witness must consent by signature (enclosure). The consent form will be kept with the Investigator performing the study. A copy of patient information sheet and signed consent form must be handed over to the patient/LAR/impartial witness.

